### General Concomitant Medications and Supportive Care Guidelines

1. Loperamide for patients with Grade II or more diarrhoea following chemotherapy.
2. Doxycycline for patients with Grade II or more rash following chemotherapy
3. Topical steroids for patients with Grade II or more rash following chemotherapy
4. Oral steroid for patients with Grade II or more nausea or vomiting following weekly methotrexate

5. Antibiotics can be administered to patients presenting with febrile neutropenia as per the institute antibiotic policy.
6. Patients should continue pre-existing medications for other comorbid conditions. However the same should be noted for any significant interactions.

### **Duration of Therapy**

Patients who have radiological progression but achieve symptomatic relief and insist on continuation of MCT may be continued the same on compassionate ground.

### **Followup**

Patients will receive MCT at 4 weekly intervals continuously till progression or intolerable side

As this is a stage I/II trial hence further followup after treatment progression will be conducted as per institutional norms.

## **11.3 Removal of Patients from Protocol**

Patients will be removed from Protocol treatment in the event of:

1. Inter-current illness that prevents further administration of treatment,
2. Participant unable to start any MCT cycle within 14 days of last cycle.
3. Toxicity which leads to discontinuation of one or more chemotherapy agents
4. Participant demonstrates an inability or unwillingness to comply with the oral medication regimen and/or documentation requirements
5. Participant decides to withdraw from the study
6. General or specific changes in the participant's condition render the participant unacceptable for further treatment in the opinion of the treating investigator.
7. Logistical constraints prevent from delivering chemotherapy e.g unavailability of chemotherapy medications or allergy to it.

The reason for study removal and the date the participant was removed must be documented in the study-specific case report form (CRF). Alternative care options will be discussed with the participant. In the event of unusual or life-threatening complications, participating investigators must immediately notify the Principal Investigator (or Protocol Chair)

In general, treatment interruptions should be avoided by preventive medical measures and nutritional, psychological, and emotional counseling. Treatment breaks, including indications, must be clearly documented on the treatment record.

### 11.4 Toxicities and Dosing Delays / Dose Modifications

All patients will be evaluable for adverse events due to chemotherapy during the study. The schedule for monitoring of adverse events is mentioned under the time and events table. All toxicities will be evaluated as per the NCI CTCAE 4.03 criteria. The final dose modification according to the following tables should be based upon the worst grade of adverse event experienced. If any of the treatment agents is held or discontinued for toxicity or intolerance, further protocol directed treatment will be stopped. Held doses of any agent will not be made up at a later date. If more than one dose reduction applies, then use the most stringent (i.e., the greatest dose reduction). Doses that are reduced at any point during a cycle will not be re-escalated. Grade I toxicities will not result in dose modifications. Patients will be removed from the protocol in the event of discontinuation of any of the agents mentioned in the protocol as per criteria mentioned below.

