### Missing dose

In case the drugs are not taken prior to breakfast then they can be taken 2 hours after food. If the dose of erlotinib or celecoxib is missed at schedule time it can be taken within 12 hours on the schedule day. However the gap between doses taken on two consecutive days should be more than 12 hours. If the dose of erlotinib or celecoxib is missed on any day then it won't be compensated. If the patient cannot take for any reason the schedule medications ( erlotinib and celecoxib ) for more than 14 days then he would be withdrawn from the protocol.

In case of oral methotrexate as it would be given weekly if the the patient misses the schedule time of 1 hour before breakfast it can be taken at any time during the schedule day. If the scheduled day is miss it can be taken administered within next 2 days.

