**Non Hematological Toxicity**

MCT has very limited non hematological side effects. The subsequent subsections show the dose modifications that should be done for derangements of metabolic parameters and non hematological toxicity during the treatment.

Nausea & Vomiting

Nausea and vomiting are unlikely. Primary prophylaxis against nausea and vomiting is not required as per the schedule mentioned in Treatment schedule above. Patients with Grade III – IV nausea and vomiting should have the dose withheld till the nausea, vomiting subsides to Grade I or less. Patients who have had one episode of Grade III / IV nausea or vomiting should have primary prophylaxis with addition of ondansetron (4 mg BD ) from the subsequent cycles of methotrexate chemotherapy. If patients continue to have Grade III- IV vomiting despite instituting antiemetic ondansetron then from the subsequent cycles of methotrexate chemotherapy additive antiemetics can be added. If in spite of high risk antiemetic prophylaxis patients continue to have vomiting ( Grade III-IV) then methotrexate should be discontinued.

Nephrotoxicity

Nephrotoxicity will be monitored in accordance with following time points

Cycle 1: Renal function test ( inclusive of serum urea, creatinine ,Na and K) for monitoring of toxicity will be done on D8 ( D7-D10)

Subsequent Cycles : Renal function test ( inclusive of serum urea, creatinine ,Na and K) for monitoring of toxicity will be done at start of each cycle.

The dose reduction in case of nephrotoxicity will be done in accordance with below mentioned table.

| Serum creatinine clearance | Methotrexate | Celecoxib  | Erlotinib          |
|----------------------------|--------------|------------|--------------------|
| > 30 ml/min                | 100 % dose   | 100 % dose | No dose adjustment |
| 15-30 ml/min               | 50% dose     | Avoid      | No dose adjustment |
| < 15 ml/min                | Avoid        | Avoid      | No dose adjustment |

Table 5: Dose reductions in case of nephrotoxicity

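### Section 11.4 ends all protocol treatment when any drug is merely held for toxicity, but the vomiting rule resumes treatment after a hold and, within a cycle, Table 5 keeps dosing the other drugs while celecoxib is avoided

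*Protocol*

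**What the plan says.** The opening paragraph of Section 11.4 sets a general rule for toxicity: "If any of the treatment agents is held or discontinued for toxicity or intolerance, further protocol directed treatment will be stopped". The next sentence adds: "Held doses of any agent will not be made up at a later date". The paragraph closes with a removal rule: "Patients will be removed from the protocol in the event of discontinuation of any of the agents mentioned in the protocol". Section 11.3 item 3 likewise names discontinuation of an agent, not a hold, as the toxicity ground for removal.

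Under Non Hematological Toxicity, the rule for nausea and vomiting has several steps. Patients with Grade III-IV events "should have the dose withheld till the nausea, vomiting subsides to Grade I or less". After one such episode they "should have primary prophylaxis with addition of ondansetron (4 mg BD ) from the subsequent cycles of methotrexate chemotherapy". If severe vomiting recurs, more antiemetics may be added. Only if it still persists, "then methotrexate should be discontinued".

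Table 5 (nephrotoxicity) has two rows at reduced creatinine clearance. At 15-30 ml/min it gives methotrexate at 50%, *Avoid* for celecoxib, and no adjustment for erlotinib. Below 15 ml/min it gives *Avoid* for methotrexate and celecoxib, and again no adjustment for erlotinib. Renal function is tested at day 8 of cycle 1 and at the start of each later cycle.

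Section 11.2 (Missing dose) withdraws a patient only after a long gap: "If the patient cannot take for any reason the schedule medications ( erlotinib and celecoxib ) for more than 14 days".

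**The concern.** The same patient can receive two opposite instructions. If Grade III vomiting has settled, the general rule says that protocol treatment is over, while the vomiting rule says to restart with prophylaxis. If clearance at day 8 of cycle 1 is found to be 15-30 ml/min, the general rule says to stop everything, while Table 5 says to continue two of the three drugs. The section has no clause saying which rule prevails, so the choice falls to whoever is treating the patient.

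These are bedside safety decisions. They also determine how much of the regimen a patient receives during the first two months, the period on which the stage 1 dose decision rests. Stage 1 has only 20-30 patients, so uneven handling of even a few is undesirable.

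**Working it through.** The protocol gives no figure to reproduce here. The check sets the rules side by side and adds a dose count as an illustration.

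**Vomiting.**
- General rule: the first hold ends protocol treatment.
- Vomiting rule: hold, recover, resume with ondansetron, add antiemetics if needed, discontinue last.
- If the general rule is applied literally, every step after the first hold is unreachable.

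**Which wording is the outlier?** Four other places assume that a hold can be followed by more treatment:
- the sentence after the general rule, on held doses, which has little purpose if treatment has ended;
- the last sentence of that paragraph, which attaches removal to discontinuation;
- Section 11.3 item 3, which does the same;
- Section 11.2, which tolerates up to 14 days without erlotinib and celecoxib, whatever the reason.

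The words *held or* therefore stand alone against the rest of the text.

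**Renal function.** Entry (Section 10.1 item 7e) and the start of every cycle (Section 11.1, item 6 of both lists) require clearance above 30 ml/min. The lower rows of Table 5 therefore matter only within a cycle, mainly at the day 8 test in cycle 1.
- At 15-30 ml/min, Table 5 continues 2 of 3 drugs and the general rule continues 0 of 3.
- Below 15 ml/min, Table 5 continues 1 of 3 and the general rule continues 0 of 3.
- If *Avoid* means a hold, the general rule conflicts with the table only through *held or*.
- If *Avoid* means discontinuation, Section 11.3 item 3 also removes the patient, and the remaining entries in those rows can never apply.

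**Dose illustration.** Table 3 gives methotrexate on D1, D8, D15 and D22, so two cycles contain 4 x 2 = 8 doses, the number that Section 11.5 also uses. Assume that methotrexate is the drug held, that the hold starts at day 8 of cycle 1, that held doses are not made up, and that nothing else interrupts treatment.
- General rule, treatment ends: D1 only = 1/8 = 12.5%.
- Restart at D15: 1 + 2 + 4 = 7/8 = 87.5%.
- Restart at D22: 1 + 1 + 4 = 6/8 = 75%.
- Restart at cycle 2: 1 + 0 + 4 = 5/8 = 62.5%.

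The vomiting rule names no restart day. It ties ondansetron to subsequent cycles, and Section 11.1 defines a cycle as 4 weeks, so the 5/8 case is as consistent with the text as the 7/8 case.

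**The case against.** The strongest reply is that the general rule may mean only a pause of all three drugs while one is held. If stopping already meant permanent removal, the separate removal sentence for discontinuation would add nothing. On that reading the vomiting conflict largely goes away. It is a possible reading, but the sentence applies one verb to held and discontinued agents alike and does not say that the stop is temporary. It also leaves Table 5 unresolved, because there the other drugs are dosed while celecoxib is avoided. A second reply, that the specific rule overrides the general one, has no support in the text, which contains no such clause.

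It is also fair to say that the cases will be few. The protocol calls nausea and vomiting unlikely, and Section 27 does not expect more renal side effects. The renal conflict requires clearance to fall to 30 ml/min or below soon after entry, and at day 8 clearance has to be calculated from the creatinine result. This limits the size of the problem but does not remove the contradiction.

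A reader might also infer that nothing limits how long methotrexate may be held, since the 14-day limit in Section 11.2 covers erlotinib and celecoxib, and the methotrexate provision there concerns only a missed day: "If the scheduled day is miss it can be taken administered within next 2 days". The document does not support that inference. Section 11.1 (item 7 for subsequent cycles) bars a new cycle until other toxicities are Grade I or less, and Section 11.3 item 2 removes a patient who cannot start a cycle within 14 days of the last. Together they cap an unresolved methotrexate hold indirectly. What is true is that no limit is stated within a cycle.

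**Conclusion.** The point holds as a contradiction in the wording of a treatment rule. The clear case is Grade III-IV nausea or vomiting. The renal case is real but confined to clearance of 30 ml/min or below found within a cycle, mainly at day 8 of cycle 1.

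Per patient, for a hold at day 8 of cycle 1, the difference is 1 of 8 methotrexate doses against about 5 to 7 of 8, under the assumptions stated with the dose count. Day 8 is the first dose that can be held after treatment starts, so this placement makes the contrast as large as it can be. The number of patients affected cannot be estimated from the protocol.

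Two further inferences should be resisted. The contradiction changes no sample size or endpoint figure. Nor does it show that all drugs ought to be held at 30 ml/min or below: that is a clinical policy choice, and the statistical point is only that the table and the removal rule should agree.

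**What to change.** 1. In the general rule of Section 11.4, delete *held or*, so that only permanent discontinuation of an agent ends protocol treatment. This agrees with the vomiting rule, the last sentence of that paragraph and Section 11.3 item 3.
2. In Table 5, state what *Avoid* means. If it is a temporary hold, the other drugs continue as tabulated. If it is a discontinuation, say that it triggers removal under Section 11.3 item 3.

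While the section is open, the team could also give the restart day after a vomiting hold. That is a clarification and not part of the contradiction.

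The cost is one short wording amendment. Section 23.2 requires a formal amendment with IRB approval for changes that may affect patient safety. No visits, tests or patients are added.

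### Section 11.4 stops all protocol treatment when any agent is held for toxicity, contradicting its own nausea and vomiting rule and the protocol's removal rules

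*Protocol*

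**What the plan says.** The general paragraph of section 11.4 sets a stopping rule for every agent and every toxicity: "If any of the treatment agents is held or discontinued for toxicity or intolerance, further protocol directed treatment will be stopped." The next sentence reads: "Held doses of any agent will not be made up at a later date." The paragraph closes on removal: "Patients will be removed from the protocol in the event of discontinuation of any of the agents mentioned in the protocol", by reference to the criteria that follow it.

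The nausea and vomiting rule, under Non Hematological Toxicity in the same section, has three steps for Grade III–IV events:

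1. Patients "should have the dose withheld till the nausea, vomiting subsides to Grade I or less".
2. After one such episode they "should have primary prophylaxis with addition of ondansetron (4 mg BD ) from the subsequent cycles of methotrexate chemotherapy". If vomiting of that grade recurs on ondansetron, further antiemetics may be added for later cycles.
3. Methotrexate is discontinued only at the last step, which begins: "If in spite of high risk antiemetic prophylaxis patients continue to have vomiting" of Grade III–IV.

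Section 11.3, item 3, lists as a ground for removal: "Toxicity which leads to discontinuation of one or more chemotherapy agents." It does not list a hold. Section 11.2, under Missing dose, withdraws a patient who cannot take erlotinib and celecoxib, whatever the reason, only when the gap exceeds 14 days.

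**The concern.** A rule that takes patients off treatment has to give one answer for one event. At a first toxicity-related hold, the general sentence ends all three drugs, while the specific rule keeps the patient on treatment with better antiemetic cover. Nothing in section 11.4 says which takes precedence.

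The reach goes beyond vomiting. Section 27 expects mucositis, loose motions and rash to increase when erlotinib is added. Section 11.4 has no hold rule of its own for these, so the general sentence would govern any hold for them. Read literally, a patient whose erlotinib is paused briefly for rash would leave protocol treatment, although the Missing dose text tolerates a gap of up to 14 days. Investigators who read the paragraph differently would treat the same event differently.

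**Working it through.** The plan gives no figure to reproduce and no arithmetic applies. The check sets the provisions side by side and asks of each whether a patient may continue after a temporary hold for toxicity.

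| Provision | After a temporary hold |
|---|---|
| 11.4, general stopping sentence | Protocol treatment ends |
| 11.4, sentence on held doses | Continues: ruling out make-up doses has a purpose only if dosing goes on |
| 11.4, closing sentence on removal | Continues: removal is tied to discontinuation |
| 11.4, nausea and vomiting rule | Continues: hold, recover, resume with antiemetics |
| 11.3, item 3 | Continues: removal is tied to discontinuation |
| 11.2, Missing dose | Continues for erlotinib and celecoxib, up to 14 days |
| 11.1, item 7 before subsequent cycles | Continues: the next cycle waits for other toxicities to reach Grade I or less |

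One provision says stop and six presuppose continuation, two of them in the same paragraph as the stopping sentence.

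Now take one patient with a first Grade III–IV vomiting episode whose dose is withheld. Under the general sentence the agent has been held for toxicity, so further protocol treatment stops. Under the specific rule the patient recovers to Grade I or less and receives ondansetron from subsequent cycles. If treatment has already stopped there are no subsequent cycles, so both cannot be followed.

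Reading *stopped* as *paused* does not remove the conflict. The sentence treats *held* and *discontinued* alike, and for a discontinued agent the closing sentence of the paragraph requires removal. The one verb cannot mean a pause in the first case and an end in the second.

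The conflict disappears if *held or* is taken out of the stopping sentence. That sentence then agrees with the other six provisions.

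One gap remains. The existing 14-day limits cover erlotinib and celecoxib (11.2) and the start of a cycle (11.3, item 2). Neither limits a methotrexate hold within a cycle, which is the situation the vomiting rule can create.

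**The case against.** The best defence is that the intent is clear. The closing sentence of the paragraph sends the reader to the criteria below it. Those include the vomiting rule, which sets its own point of discontinuation. A specific rule following a loosely worded general sentence would ordinarily be preferred, and the other provisions agree with it. This stands as far as intent goes and is why the severity is low. It does not make the sentence correct: the sentence applies to any agent, states no exception, and is the only text on a hold for toxicities that have no specific rule.

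It is also fair that the event may be rare. Section 11.4 calls nausea and vomiting unlikely. With weekly methotrexate, vomiting may settle before the next dose is due, in which case no methotrexate dose is held.

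A reader might infer three stronger points that the documents do not support:

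- **Distorted endpoints.** Early stopping could be thought to bias Stage 1 dose selection or Stage 2 progression-free survival. Under section 16.1 stopping drug is not an endpoint event, so any effect would be indirect, and the protocol gives no rate of holds from which to size it.
- **A count of lost doses.** The protocol gives no duration for a hold, and zero lost methotrexate doses is possible. Any count would rest on assumption alone.
- **A second contradiction in Tables 5 and 6.** *Avoid* is not defined there as either a hold or a discontinuation, so a conflict is not established. Section 11.1 already bars a new cycle unless creatinine clearance is above 30 ml/min.

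**Conclusion.** The contradiction is real and confined to one sentence. As written, section 11.4 ends protocol treatment at a hold, against the vomiting rule and the rest of the protocol's text on holds and removal. The correct meaning can be recovered from the surrounding text, so this is a low-severity inconsistency that should be corrected because it sits in an operative stopping rule. No sample size, error rate or analysis is affected. The number of patients concerned and any effect on dose selection or progression-free survival cannot be computed and are likely small. The conclusion rests on reading *held* as a temporary interruption, which is how the sentence on held doses uses it.

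**What to change.** In the stopping sentence of section 11.4, delete *held or* and insert *permanently* before *discontinued*. Then add a sentence stating that temporary holds for toxicity are allowed up to the protocol's existing 14-day limit, and that this limit also applies to methotrexate holds within a cycle. The added sentence is needed because the present limits do not cover that case. With weekly dosing, 14 / 7 = 2, so at most two consecutive methotrexate doses could be withheld if the limit is counted from the scheduled day of the first one.

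Keeping *held* but restricting it to holds longer than 14 days would also remove the conflict. The vomiting rule, section 11.3 and the dose tables need no change for this point.

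The cost is a wording change in one paragraph of a protocol amendment, with no extra patients, visits or tests.

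### Section 11.4 ends protocol treatment whenever an agent is held for toxicity, against the rest of the protocol, and leaves the Table 5 row for 15-30 ml/min unusable

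*Protocol*

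**What the plan says.** The opening paragraph of Section 11.4 holds three statements that bear on a hold:

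- the stop rule: "If any of the treatment agents is held or discontinued for toxicity or intolerance, further protocol directed treatment will be stopped";
- directly after it: "Held doses of any agent will not be made up at a later date";
- at the end: "Patients will be removed from the protocol in the event of discontinuation of any of the agents mentioned in the protocol".

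Section 11.3 lists the grounds for removal. Item 3 is "Toxicity which leads to discontinuation of one or more chemotherapy agents", and item 2 is "Participant unable to start any MCT cycle within 14 days of last cycle". Section 11.2, under Missing dose, adds a general rule for erlotinib and celecoxib: "If the patient cannot take for any reason the schedule medications" "for more than 14 days then he would be withdrawn from the protocol".

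Section 11.1 makes each later cycle conditional on recovery of other toxicities to Grade I or less and on a calculated creatinine clearance above 30 ml/min. The note to Table 3 in 11.2 also makes repeat cycles wait for toxicity to resolve.

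The vomiting rule in 11.4 is a ladder: withhold at Grade III-IV until Grade I or less, then give ondansetron from the next cycles, then add further antiemetics, and discontinue methotrexate only if all this fails.

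For a creatinine clearance of 15-30 ml/min, Table 5 gives methotrexate at 50%, marks celecoxib as Avoid and leaves erlotinib unchanged.

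**The concern.** A hold and a discontinuation are different acts, and the stop rule treats them alike while the surrounding rules keep them apart. Staff who withhold a dose for Grade III-IV vomiting, or erlotinib for a rash, cannot tell from the protocol whether the patient pauses or is off treatment.

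The situation is foreseeable. Section 27 expects more mucositis, loose motions and rash once erlotinib is added, and Section 11.4 has no dose table for any of them. A hold for one of these reactions therefore falls between the stop rule in 11.4 and the 14-day allowance in 11.2.

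The stakes are clinical first. Patients are enrolled with a life expectancy under 6 months on standard palliative treatment (Section 10.1, item 6), and the rule that is followed decides whether they stay on therapy. In addition, Table 5 read alone tells staff to give methotrexate at a clearance where 11.1 would not let the cycle begin.

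**Working it through.** No sample size, power or event figure bears on this point, so there is no figure to reproduce. The check sets the rules side by side.

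**1. What happens after a toxicity hold?**

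| Place | Consequence of a hold |
|---|---|
| 11.4, stop rule | Protocol treatment ends |
| 11.4, next sentence | Skipped doses are not made up, which has a purpose only if treatment goes on |
| 11.4, closing sentence | Removal is tied to discontinuation; holds are not named |
| 11.3, item 3 | Toxicity removal only on discontinuation |
| 11.3, item 2 | A cycle may be delayed, up to 14 days |
| 11.1 and note to Table 3 | The next cycle waits for recovery, then proceeds |
| 11.2, Missing dose | Withdrawal only after more than 14 days without erlotinib and celecoxib, whatever the reason |
| 11.4, vomiting | Withhold, recover, continue with prophylaxis |

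The vomiting ladder decides the matter. Under the stop rule the patient leaves treatment at the first withheld dose, so ondansetron prophylaxis, the added antiemetics and the final discontinuation step could never be reached. The 11.2 rule gives the same conflict in days: a toxicity hold of erlotinib and celecoxib lasting 1 to 14 days ends treatment under 11.4 and does not under 11.2.

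**2. Can the Table 5 row for 15-30 ml/min ever be applied?** Renal function is scheduled on day 8 of cycle 1 and at the start of each later cycle.

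- *Start of a cycle:* 11.1 requires clearance above 30 ml/min. The whole row lies at or below 30, so the cycle cannot start.
- *Day 8 of cycle 1:* no cycle-start limit applies, but avoiding celecoxib is either a hold or a discontinuation. The stop rule ends treatment on both, and item 3 of 11.3 also removes the patient if it is a discontinuation.

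The 50% methotrexate dose can therefore not be given on protocol at either time.

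**3. Table 6, for comparison.** Its first row covers bilirubin 2-4 x ULN and/or ALT/AST above 4 x ULN, with doses of 75% (methotrexate), 50% (celecoxib) and 50% (erlotinib). The 11.1 limits for later cycles are below 1.5 x ULN and below 2.5 x ULN, so this row cannot apply at a later cycle start while the abnormality lasts. Table 7, however, also schedules liver function on day 8 of cycle 1. There no cycle-start limit applies and the row holds no agent, so it can be used directly. The second row avoids all three agents and works as a stop rule. ALT/AST above 4 x ULN appears in both rows.

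**4. Cross-reference.** The haematological text in 11.4 sends the reader to Table 6, but the haematological doses are in Table 4.

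**The case against.** The best defence of the stop rule is that it is the specific rule for toxicity, while the 14-day allowance in 11.2 is a general rule under a heading about missed doses, so the specific rule should govern. That weakens 11.2 as evidence. It does not rescue the rule, because the vomiting ladder is just as specific to toxicity and stands in the same section, and the paragraph's own next and last sentences pull the other way.

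Several stronger readings are tempting, and the protocol does not support them:

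- *That Table 6 works only as an unstated restart dose.* Its first row can be applied to the day 8 liver tests. The note to Table 3 (resolve, then modify) and the 11.4 instruction that modifications be "based upon the worst grade of adverse event experienced" largely supply the order for later cycles.
- *That ALT/AST above 4 x ULN leaves methotrexate at either 75% or nothing.* Section 11.4 also says that the most stringent reduction applies when several do, which most naturally gives Avoid. What remains is a cell in the first row that never operates.
- *That bilirubin 1.5-2 x ULN and ALT/AST 2.5-4 x ULN are gaps needing new doses.* Section 11.1 delays the cycle until recovery and no reduction is specified. That is coherent.
- *That the clearance limit in 11.1 cannot be checked, because 11.4 omits clearance from pre-cycle monitoring unless Grade II renal toxicity has occurred.* Creatinine is drawn at the start of each later cycle, so clearance can be calculated. The text needs only a clarification.

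**Conclusion.** The point stands as an internal contradiction in Section 11.4, with two parts: the inclusion of holds in the stop rule, and the Table 5 row for 15-30 ml/min, which cannot be given on protocol. Both follow from the text alone. The first assumes that a withheld dose in the vomiting rule is a hold in the sense of the stop rule. The second assumes that avoiding celecoxib counts as holding or discontinuing it.

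The size cannot be put as a number of patients, since the protocol gives no frequency for these toxicities. In the individual case the difference is between resuming and ending therapy. A reader might infer that the stage 2 PFS estimate or sample size is compromised. Nothing in the document allows that to be shown, and it is not claimed. The correction should be made because it is specific, cheap and settles who stays on treatment.

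**What to change.** Main changes to Section 11.4:

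1. Delete the words *held or* from the stop rule, so that only discontinuation ends protocol treatment. State that a toxicity hold of up to 14 days, in line with 11.2 and 11.3, does not.
2. State whether avoiding celecoxib at 15-30 ml/min is a temporary hold or ends protocol treatment, and align that Table 5 row with the limit above 30 ml/min in 11.1. This does not call for holding erlotinib, which Table 5 leaves unadjusted, or for a new methotrexate restart dose.

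Minor corrections in the same amendment:

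- List ALT/AST above 4 x ULN in one row of Table 6 only; the investigators should confirm the intended cut.
- Say that at later cycle starts the first row of Table 6 applies once the 11.1 limits are met again.
- Clarify under Hepatic Dysfunction that clearance is calculated before each cycle from the creatinine already drawn.
- Correct the haematological cross-reference from Table 6 to Table 4.

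No new blood tests or patients are needed. The text changes are short, but they bear on patient safety and study procedures, so Section 23.2 requires a formal amendment with institutional review board (IRB) approval.
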